### Data collection

Data for this clinical trial will be collected and documented on specially designed subject Case Report Forms (CRFs) provided digitally. Authorized study site personnel will complete CRFs only. CRFs will be reviewed and signed by the Investigator or his/her designees. Since there is a potential for errors, inaccuracies, and misinterpretation in transcribing data onto the CRFs, the following documents are available at all times for inspection and comparison to the CRFs by the study monitor where appropriate: data query forms, originals and certified copies of all relevant records and reports, copies of test results. On CRFs and patients’ cB + cBMA samples, patients will not be identified by their names but by an anonymized code. The subject identification code list will be safeguarded by the investigator only.

### Data acquisition and follow-up

Participating patients will be assessed at the following time points (Table 1):

**Table 1 Tab1:** Schedule for screening and follow-up of included participants

Screening and Follow-Up Clinical and Radiographic Exams						
Action	Pre-operative	Intra-operative	Follow-Up Visit (biweekly 2-14 weeks)	Follow-Up Visit Until Union (biweekly) (>14 weeks, determined by physician)	6 month follow-up visit	1 year Follow-Up visit
Information letter	X					
Obtain written informed consent	X					
Complete eligibility checklist	X					
Complete medical history and baseline characteristics (form)	X					
Complete physical examination (form)	X		X	X	X	X
Surgery		X				
- Operative form (surgical information)		X				
- cB + cBMA preparation and administration		X				
- Bone biopsy fracture site		X				
Lab assessments	X					
Questionnaires	X		X		X	X
Radiographic assessment	X	X	X	X	X	X
Complication (form)	X	X	X	X	X	X
Adverse events, withdrawals & re-operation (form)	X	X	X	X	X	X

before inclusion: information letter, complete reliability checklistpreoperatively (after an enrollment period of two weeks): informed consent, complete reliability checklist, baseline characteristics (age, gender, weight, height, affected side, duration of symptoms, smoking status, AAS before symptoms and at preoperative assessment, past medical history, medication used), type of sport and profession, local physical examination with VAS, laboratory assessment (Hemoglobin levels, leucocytes, sodium, potassium, urea and creatinine), FAOS, FAAM, SF-36, EQ-5D, SF HLQ, X-ray (AP oblique and lateral);intraoperative: cB + cBMA preparation and administration, bone biopsy of the fracture site, right after internal fixation an X ray (AP, oblique and lateral) and an operative form (surgical information) with complications and (S)AEs if applicable;biweekly 2-14 weeks postoperatively: wound inspection, local physical examination with VAS, FAOS, FAAM, SF-36, EQ-5D, TiC, X-ray (best view for analyzing the fracture), resumption of sports and work, complications and (S)AEs;six months postoperatively: local physical examination with VAS, FAOS, FAAM, SF-36, EQ-5D, TiC, X-ray (best view for analyzing the fracture), resumption of sports and work, complications and (S)AEs;one year postoperatively: local physical examination with VAS, FAOS, FAAM, SF-36. EQ-5D, TiC, X-ray (best view for analyzing the fracture), resumption of sports and work, complications and (S)AEs

If union is not yet achieved after 14 weeks, patients are seen as determined by the responsible physician. At every subsequent visit at least an X-ray is made to be able to evaluate the status of the fracture (primary outcome).

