## Background

Marines, soldiers and athletes are prone to fractures due to extensive and repeated stress on (usually weight bearing) bones [1–4]. These stress fractures develop over time and are therefore different than the more commonly accounted traumatic fractures. The damage caused by repeated forces on the bone outruns the natural remodeling process in loaded bones, resulting in a weak spot or ‘stress reaction’ and eventually a stress fracture [5–7]. Due to the increasing sports participation in the general population and awareness of their existence, these types of fractures are more frequently diagnosed. Of all stress fractures of the lower leg, the stress fracture of the fifth metatarsal has one of the highest incidences, namely up to 25 % [8]. This issue is amplified in the patients that depend on perfect physical condition like professional athletes. In a recent review of the literature, it is described that operative treatment of fifth metatarsal stress fractures results in smaller number of delayed unions or non-unions, compared to conservative treatment [9]. Still, the time to return to activity varies from 12 to 18 weeks [9–12].

Compared to a normal, traumatic fracture, stress fractures do not seem to heal via callus formation, but rather by primary bone healing with remodeling across the fracture line [7, 13, 14]. This process is slower with a higher propensity to fail, resulting in a complete fracture and refractory healing, similar to non-union [7, 14]. In traumatic fractures healing starts with formation of hematoma and therewith release of inflammatory cells. The next phase is recruitment of mesenchymal cells that differentiate into osteoblasts resulting in primary bone formation with callus production followed by secondary bone formation, with bone remodeling. In stress fractures, healing starts with the remodeling phase. Via early woven bone formation, callus is only formed along the exit point of the fracture towards the medullary cavity [15, 16].

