## Definitions

### Primary outcome

The primary outcome will be assessed on X-ray in different directions; on AP view, lateral view and an oblique view. The following will be scored by two single blinded evaluators (skeletal radiologist and orthopaedic surgeon): correct position osteosynthesis (yes/ no), fracture line visible (yes/ no), % of fracture line visible, union (yes/ no).

The X-rays will be acquired every 2 weeks until the 14^th^ week and, after that, only in the patients in which radiological union has not yet occurred as deemed necessary by the treating physician.

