### Secondary outcomes

Clinical union will be measured during physical examination. Pain on axial compression force and pain on the fracture site during palpation will be monitored through a patient-based VAS score. When patients still report significant pain, measured as a VAS > 3 on a Visual Analogue Scale from 0 to 10 [31, 32], clinical union is not yet achieved. Return to sports is defined as the time (in weeks) to resumption of weight-bearing sports after surgery and the level should be maintained for at least 30 days [33]; return to work is defined in the same way. When returned to sport, but activity level decreases to below the start level within 30 days after resumption, then this will be deemed as a failed return to activity and the date will not be counted. From the 6^th^ till the 14^th^ week, most unions are expected to occur. On each of these biweekly time points a union rate will be counted; number of unions at t = XXX divided by total sample size (%).

The SF-36 is a patient-administered, generic health related quality of life instrument [34, 35]. The FAOS was developed to assess the patients’ opinion about a variety of foot and ankle-related problems [36]. The results can be presented as an outcome profile. The FAAM is a 29-item questionnaire. The FAAM consists of 2 subscales: Activities of Daily Living and Sports [37].

Cost-effectiveness is analyzed using the The EuroQol (EQ-5D) [38, 39] and the SF-36, FAOS, FAAM as measurement for effectiveness of treatment. Costs are calculated from the SF HLQ [40, 41] and the cost of the investigated intervention. The questionnaire consists of 11 questions and provides information about labor (missing) costs and additional paid working hours.

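### After week 14, whether clinical union is still examined before month 6 depends in effect on radiological union, so this secondary endpoint is observed coarsely and unequally by arm, with a bias of uncertain direction

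*Protocol article*

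**What the plan says.** **Visits.** Data acquisition and follow-up (Protocol article) plans visits every two weeks from week 2 to week 14, then at 6 months and 1 year. For the period between, its closing paragraph states: "If union is not yet achieved after 14 weeks, patients are seen as determined by the responsible physician". It requires at least an X-ray at each such visit, for the primary outcome. Definitions, Primary outcome, limits X-rays after week 14: "only in the patients in which radiological union has not yet occurred as deemed necessary by the treating physician". The matching column of Table 1 is headed as visits until union, both biweekly and determined by the physician. It ticks the physical examination but not the questionnaires.

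**Clinical union.** Definitions, Secondary outcomes, has it measured at physical examination and not achieved while VAS exceeds 3. Statistical methods gives it the same analysis as the primary endpoint, Student's t-test or an equivalent.

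**Return to sport and work.** This is the time from surgery to resumption, and "the level should be maintained for at least 30 days"; the date of a failed return is not counted. Resumption is asked about at the biweekly visits to week 14, at 6 months ("six months postoperatively: local physical examination with VAS, FAOS, FAAM, SF-36, EQ-5D, TiC, X-ray (best view for analyzing the fracture), resumption of sports and work") and at 1 year. It is not listed for the extra visits. The Background gives the expected timing: "Still, the time to return to activity varies from 12 to 18 weeks".

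**The concern.** Clinical union can be seen only when someone examines the patient. If extra examinations after week 14 are triggered by missing radiological union, the precision of this secondary endpoint is set by the primary outcome, which the treatment is meant to change. A patient united on X-ray at week 10 but still painful at week 14 is next examined at about week 26, even if the pain settles at week 15. A patient not yet united on X-ray may be examined at week 16 or 18. The two arms would then be measured on different grids, and a t-test on visit weeks would mix the treatment effect with the visit pattern.

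Return to sport raises a lesser question. Activity is expected to resume around and just after week 14, when planned questioning stops until month 6, and quicker return is one of the trial's stated hypotheses.

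**Working it through.** **1. The plan's own figure.** Sample size gives means of 12 and 10 weeks, SD 1.88, 5% significance and 90% power. Two-sided, n = 2 × (1.960 + 1.282)² × 1.88² / 2² = 18.6, so 19 per arm. The t-based calculation gives 19.6, so 20, and 20 / 0.80 = 25. The stated 20 and 25 reproduce. Neither depends on visits after week 14.

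**2. Who has no planned visit between week 14 and month 6.** Take radiological union as normal with the same means and SD.
- Control: P(not united at week 14) = 1 − Φ((14 − 12)/1.88) = 1 − Φ(1.064) = 14.4%.
- Intervention: 1 − Φ((14 − 10)/1.88) = 1 − Φ(2.128) = 1.7%.

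So 85.6% of controls and 98.3% of intervention patients have no planned examination for 26 − 14 = 12 weeks.

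**3. Effect on recorded clinical union.** The article gives no distribution for clinical union, so its means (12 to 18 weeks), its SD (1.88) and its correlation with radiological union (0, 0.5, 0.8) are assumptions. One million patients per arm were simulated, with radiological union at 12 vs 10 weeks throughout. Visits were every two weeks to week 14, then every two weeks until radiological union in those not united, and at weeks 26 and 52. Clinical union was recorded at the first visit at or after it occurred. Ranges are over the three correlations. A positive difference favours the intervention. Power is a normal approximation at 20 per arm, two-sided 5%.

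| Clinical union, control vs intervention (weeks) | True difference | Recorded difference | In the gap, control / intervention | Power |
|---|---|---|---|---|
| 12 vs 10 | 2.0 | 2.54 to 3.06 | 7–13% / 1–2% | 0.71–0.73 |
| 14 vs 12 | 2.0 | 4.65 to 4.78 | 43–45% / 14% | 0.75–0.77 |
| 16 vs 14 | 2.0 | 4.07 to 4.53 | 80–85% / 49–50% | 0.64–0.75 |
| 18 vs 16 | 2.0 | 1.38 to 1.56 | 96–98% / 85–86% | 0.25–0.33 |
| 12 vs 12 | 0 | −0.17 to −0.68 | 7–13% / 14% | – |
| 14 vs 14 | 0 | −0.48 to −0.63 | 43–45% / 49–50% | – |
| 15 vs 15 | 0 | −0.25 to −0.55 | 64–68% / 70% | – |

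With two-weekly examination continued for everyone until clinical union, the recorded difference equals the true one, the SD is about 1.97 weeks, and power for a true 2 weeks is about 0.90. Under the planned schedule at 12 vs 10, the SD is 3.7–4.7 weeks in controls and 2.4–2.7 in the intervention arm.

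**4. Why the sign changes.** If clinical union speeds up along with radiological union, more controls jump to week 26 and the benefit is exaggerated. If clinical union is the same in both arms, controls not united on X-ray keep being examined, fewer of them jump, and the intervention looks worse. If clinical union is late in both arms, nearly everyone is recorded at week 26 and the difference shrinks.

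**5. Return to sport.** A return at week 15 that is first asked about at week 26 has its date and 30-day status recalled 11 weeks later. Resumption is not listed for the extra visits, so planned collection is the same whether or not the patient is united on X-ray.

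**The case against.** **The trigger.** The closing paragraph of Data acquisition and follow-up and Table 1 say only union, in a protocol that defines both radiographic and clinical union. The explicit restriction to radiological union concerns X-rays. This stands as an ambiguity. The compulsory X-ray for the primary outcome at each extra visit still points to radiological union, and no text provides a visit for a patient united on X-ray but still painful.

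**The coding.** No passage says that clinical union is recorded as week 26. The t-test may be replaced by an equivalent, and an analysis plan not shown could specify interval censoring. This stands too: the recorded differences above apply only if the visit week is used as the event time. An analysis plan cannot restore examinations that never took place, however, and the article does fix the schedule.

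**The direction.** A reader might infer that the schedule penalises the faster-healing arm. The documents do not support that. It needs clinical union to be equal in both arms, or very late in both. If clinical union follows the trial's own hypothesis of faster healing, the schedule mostly exaggerates the benefit.

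**Return to sport.** A reader might also infer that returns are shifted to week 26, or that only those before week 9.7 (14 − 30/7) count. Neither follows. The endpoint is a date, which can be given at the 6-month visit, and nothing requires the 30 days to be complete by week 14. No arm bias is shown.

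**Conclusion.** The point holds for time to clinical union. Under the radiological reading, a patient united on X-ray but with VAS above 3 at week 14 has no planned examination until month 6. The share of patients with no visit in the gap differs by arm, about 86% vs 98% on the plan's own figures and a normal distribution.

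If visit weeks are compared by t-test, the result is noisy and biased, and the direction cannot be known in advance. The size rests on assumed clinical-union means and correlations, on the plan's SD carried over to clinical union, and on extra visits every two weeks although the text leaves timing to the physician. The article expects most unions between weeks 6 and 14; if clinical union is that early, the milder rows (12 vs 10, 12 vs 12) are the relevant ones.

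For return to sport and work, only recall of the date and weak checking of the 30-day rule remain. The primary endpoint and the sample size are not affected. This is worth correcting for the secondary endpoints; it is not a threat to the main result.

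**What to change.** 1. State which union triggers visits after week 14, and reconcile Table 1 (biweekly) with the text (physician-determined).
2. Make the clinical-union assessment independent of radiological union: for endpoint purposes, continue the VAS examination on one schedule for all patients until clinical union, without an added X-ray.
3. If extra examinations are not acceptable, at minimum replace the t-test on visit weeks. Analyse time to clinical union as interval-censored between the last visit with VAS > 3 and the first with VAS ≤ 3. This handles the uneven visit grid but does not recover the lost precision.
4. Between week 14 and month 6, collect the calendar date of sport and work resumption and its 30-day status from all patients, by a short digital or telephone form.

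The cost is a few short contacts per patient, some brief examinations for those still painful at week 14, and slightly more analysis work. No extra patients or films are needed. Two-weekly in-person examination is the most burdensome option; items 3 and 4 are the cheap minimum.

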## Withdrawal of subjects

Subjects can leave the study at any time for any reason if they wish to do so, without any consequences. The investigator can decide to withdraw a subject from the study for urgent medical reasons. Subjects will not be replaced after withdrawal. Data of a withdrawn subject will be used, but we will delineate from which visit (time point) data is incomplete and (if known) why the subject is sequestered. To investigate why subjects are withdrawn, they will be contacted by telephone and/or letter to assure the reason for their withdrawal and to ask them to come in for an optional final visit.

## Sample size

The sample size calculation was performed based on time to radiological union. Significance level was set at p < 0,05. In recent studies, the mean time to union was 12 weeks [11, 12]. We argue that reducing this with 2 weeks would be clinically relevant: Group 1 (without cB + cBMA) has a mean of 12 weeks, group 2 (with cB + cBMA) a mean of 10 weeks. As the standard deviation is difficult to determine, we estimated SD with use of the method described by Walter and Yao [42], which resulted in an SD of 1.88 weeks.

To achieve a power of 90 % (with an effect size of 1,06) we need a number of 20 patients in each group. Taking into account a possible dropout-rate of maximally 20 %, we need 25 patients in each randomization arm. This calculation will be validated and altered as needed after the interim analysis according to O’Brien [43] and performed when 10 patients enrolled in each arm (40 %) have reached the 14 weeks’ time point. This analysis reduces the significance of the final comparison of the primary outcome to *p* = 0.049. When a difference of ≥3 weeks between the means of the primary outcome among the groups is detected (SD 1.88) at the interim analysis; a significance is already found (*p* = 0.003).

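### The interim efficacy criterion is a fixed 3-week mean difference at an assumed SD of 1.88; it should be a p-value boundary on the observed data

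*Protocol article*

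**What the plan says.** Everything needed is in the Sample size section of the protocol article. The overall level is fixed first: "Significance level was set at p < 0,05". The planning means follow: "Group 1 (without cB + cBMA) has a mean of 12 weeks, group 2 (with cB + cBMA) a mean of 10 weeks". The SD is not an observed one. The section introduces it with "As the standard deviation is difficult to determine" and reports an indirect estimate, "which resulted in an SD of 1.88 weeks". The size is then given: "To achieve a power of 90 % (with an effect size of 1,06) we need a number of 20 patients in each group", raised to 25 per arm for 20% dropout.

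One O'Brien-type interim analysis is planned, "performed when 10 patients enrolled in each arm" (labelled 40%) have reached 14 weeks. For the end of the trial, "This analysis reduces the significance of the final comparison of the primary outcome to" 0.049. The interim criterion reads "When a difference of ≥3 weeks between the means of the primary outcome among the groups is detected (SD 1.88) at the interim analysis", in which case significance is already found, with p = 0.003 in brackets.

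The Statistical methods section names a Student's t-test or equivalent for the primary endpoint. It promises an updated sample size justification and statistical plan, to be written after the interim analysis.

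**The concern.** A group-sequential boundary limits false positive claims because it is set on a test statistic or p-value, which scales the observed difference by the observed spread. A cut-off on the raw difference does this only at the SD for which it was worked out. Here that SD is one the protocol itself describes as hard to establish. If time to union varies more than assumed, a 3-week difference between two groups of 10 is weaker evidence than the sentence claims, and efficacy could be declared after 20 patients on a result that does not reach 0.003.

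A second, smaller point lies next to it. The printed percentage and the printed levels use different denominators, so a reader cannot tell which information fraction the boundary was built for.

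**Working it through.** **Inputs (Sample size section).** Means 12 and 10 weeks, SD 1.88, overall level 0.05 (sidedness not stated; two-sided reproduces the sample size), 90% power, 20 evaluable and 25 randomized per arm, interim at 10 per arm, levels 0.003 and 0.049.

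**1. The plan's own figures reproduce.**
- Effect size: 2/1.88 = 1.06. The two-sided t-test needs 19.58, so 20 per group; power at 20 is 90.6%. Dropout: 20/0.8 = 25.
- Levels: Lan-DeMets spending of O'Brien-Fleming type, 0.025 per side, at information fraction t spends 2 × 2[1 − Φ(z₀.₀₁₂₅/√t)] at the interim. At t = 0.50 this is 0.00305, and the final level that brings the total to 0.05 is 0.0490. These match 0.003 and 0.049.

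**2. What a 3-week difference means at 10 per arm.**
- At SD 1.88: standard error 1.88 × √(2/10) = 0.841; t = 3/0.841 = 3.57 on 18 df; two-sided p = 0.0022. This passes 0.003.
- The two-sided 0.003 critical value on 18 df is 3.428. The smallest passing difference at SD 1.88 is 3.428 × 0.841 = 2.88 weeks.
- The largest observed SD at which 3 weeks passes is 3/(3.428 × √0.2) = 1.96, about 4% above the planning value.

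**3. The cut-off applied literally.** Suppose efficacy is claimed at the interim whenever the absolute difference is at least 3 weeks, and otherwise the final test is made at 0.049. Under no effect and normal data, the chance of a false interim claim is 2[1 − Φ(3/(σ√0.2))]. Overall alpha comes from simulation (400,000 runs per setting). The ranges cover a final 20 or 25 per arm and simulation error. SDs other than 1.88 are assumptions, because the protocol gives no other value. The SD in the first column is the observed SD for the p-value and the true SD for the other columns.

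| SD (weeks) | p for an observed 3-week difference | False interim claim | Overall alpha, 3-week rule | Overall alpha, p ≤ 0.003 rule |
|---|---|---|---|---|
| 1.88 | 0.0022 | 0.0004 | about 0.049 | 0.050-0.051 |
| 2.5 | 0.015 | 0.007 | 0.052-0.054 | 0.050-0.051 |
| 3.0 | 0.038 | 0.025 | 0.064-0.067 | 0.050 |
| 4.0 | 0.11 | 0.094 | 0.12 | 0.050-0.051 |

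The last column shows that a p-value boundary on the same data holds alpha at every SD.

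**4. The information label.** 10/25 = 40% of those randomized; 10/20 = 50% of the evaluable patients behind the power calculation. From the bivariate normal with correlation √t, the pair 0.003/0.049 has overall alpha 0.0500 at t = 0.50 and 0.0504 at t = 0.40. If 40% information were intended, the levels would be about 0.0008/0.0497 (Lan-DeMets form) or 0.0019/0.0492 (classical form).

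**The case against.** The best defence is that the sentence only illustrates what would reach 0.003 if the planning SD were right. It carries both the SD and the p-value in brackets, and the Statistical methods section specifies a t-test, which uses the observed SD. Read so, the boundary is p = 0.003 and alpha is controlled. The wording allows this, and nothing in the document says that the 3-week figure overrides the test. But no other sentence states an interim rule, so the document does not settle which reading governs. An unseen analysis plan might settle it; even so, the sentence as printed can be applied literally, and the updated plan that the article promises comes only after the interim.

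It is also fair that the larger figures need two things together: literal use of the cut-off and a true SD well above 1.88. At 1.88 the literal rule is conservative, and at 2.5 the excess is small. A 3-week difference with p above 0.05 needs an observed SD above about 3.19 (3/(2.101 × √0.2)).

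Three stronger readings are tempting, and the documents do not support them:
- *That the 40% label shows alpha to be uncontrolled.* As an enrolment fraction 40% is correct, the levels fit 10 of 20 evaluable, and even at a true 40% the excess is 0.0004.
- *That p = 0.0022 contradicts the printed 0.003.* Taken as the threshold, 0.003 is passed by 0.0022, so the sentence is true at SD 1.88.
- *That no interim mean can be formed because some patients have not united by week 14.* No section says such patients are dropped, X-rays continue after week 14 where union is absent, and patients enrolled earlier may have longer follow-up. How un-united patients enter the analysis is a separate question; under the planning assumptions, dropping them would shrink the difference and cost power rather than inflate alpha.

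**Conclusion.** The point holds in a narrow form. The only interim efficacy criterion in the protocol article is a raw 3-week difference at an assumed SD, and it corresponds to 0.003 or better only for an observed SD up to about 1.96. If the cut-off is used literally, overall alpha runs from about 0.049 at SD 1.88 to about 0.12 at SD 4. That range rests on normal data, 10 per arm at the interim, a final test at 0.049, and SDs that are assumptions beyond 1.88. If the sentence is an illustration and the decision rests on p ≤ 0.003, alpha is held at about 0.05. The fault is that the document leaves this open for a decision threshold. A reader might infer that the design as a whole fails to control alpha; the levels themselves are sound, and the 40%/50% discrepancy is one of labelling.

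**What to change.** Before any interim data are examined:
- Replace the 3-week criterion with a two-sided p-value boundary for the primary test, computed from the observed data: p at or below 0.003 at the interim and 0.049 at the end. If the 3-week figure is kept, mark it as an illustration at the planning SD.
- Name the O'Brien-Fleming-type spending function (the Lan-DeMets form reproduces the printed levels).
- State the information fraction as 10 of 20 evaluable per arm, 50%. If 10 of 25 is meant, recompute the levels (about 0.0008 and 0.0497).

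The cost is protocol wording, with no change in sample size. The interim bar becomes stricter if the observed SD exceeds about 1.96. Below that it is slightly easier, for example 2.88 rather than 3 weeks at SD 1.88.
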